### Data analysis

Results will be reported in accordance with the Consolidated Standards of Reporting Trials extension to randomised pilot and feasibility trials^30^ and the Consolidated Criteria for Reporting Qualitative Research.^31^

For each of recruitment, retention and outcome measure completion data, rate (as a percentage) and corresponding 95% CI will be computed. Outcomes data (including health economic data) will be analysed descriptively by an appropriate member of the research team using means, range and measures of variance (CIs, SD) for continuous variables, and count (n) and percentages (%) for categorical variables. Distribution of DAOH-30 and DAOH-90 data will be explored to determine the best model to use to analyse them (eg, whether t-test or a model for count data) and to plan a definitive RCT.

Intervention fidelity will be assumed if 70% of planned sessions are completed from those available and broken down by facilitator to examine variation between provider sites. During fidelity scoring, examples of good practice will be identified for training during the main trial. A traffic light system shown in table 2 that is recommended for best practice will be used as a guide for progression to a definitive trial.^32^

**Table 2 T2:** ‘Traffic light’ system to determine progression to a definitive trial

	Green(trial feasible)	Amber(may be feasible with modification)	Red(likely unfeasible)
Recruitment of proposed rate (%)	100%(60 participants)	99%(36–59 participants)	<60%(<36 participants)
Retention rates—defined as collection of primary outcome measure (days alive and out of hospital)	100%(60 participants)	60–99%(36–59 participants)	<50%(<36 participants)
Intervention fidelity (physiotherapy)Proportion of available sessions completed	> 70%	40–70%	<40%
Intervention fidelity (nutrition)Proportion of prescribed supplements taken	>70%	40–70%	< 40%

Verbatim anonymised transcripts of semistructured interviews will be thematically analysed.^33^ Codes and themes will be identified from the data and refined using an iterative process. Analysis of interview transcripts will be supported by NVivo V.12 (NVivo qualitative analysis software; QSR International V.12).

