### Sample size

Since this is a feasibility study, the sample size is not determined by a power calculation but rather aims to estimate the rate of recruitment and retention to inform the future trial. We aim to recruit a total of 60 patients, with an equal number (maximum of n=30) from each site and equal random allocation to control and intervention groups. The sample size enables a high probability of continuing to a definitive RCT. For example, for retention rate, progression to definitive RCT will be considered if the estimate is ≥40%. The probabilities of getting a retention estimate ≥40% in each group when the true rates are 50% (low rate) and 80% (a good rate in definitive RCTs) are 0.82 and 1, respectively, which are high. We estimate that we will have sufficient data to identify key issues and themes after having interviewed approximately five members of staff and eight patients from each site unless saturation is deemed to be achieved before this point.

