### Assignment of interventions

#### Randomisation

Participants will be randomised in a 1:1 ratio to either the intervention or standard care group using an electronic randomisation system, which will facilitate allocation concealment. Randomisation will be stratified by study site.

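### The retention row of Table 2 conflicts with itself and with the rest of the protocol: green needs 100%, the counts assume 60 randomised, and the red band does not fit its own count or the 40% progression rule

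*Protocol article*

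**What the plan says.** Data analysis, Table 2. The row is headed "Retention rates—defined as collection of primary outcome measure (days alive and out of hospital"). Its bands are:

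- green: "100%(60 participants");
- amber: 60–99%, 36 to 59 participants;
- red: below 50%, fewer than 36 participants.

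The counts are the same as in the recruitment row above it. The text introducing the table presents it as a guide to progression, and says that retention will be reported as a percentage with a 95% CI.

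Primary outcome measures. Retention is a proportion of participants, namely those who complete the primary outcome. Nothing there fixes the denominator at 60.

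Sample size. The target is 60: "We aim to recruit a total of 60 patients, with an equal number (maximum of n=30) from each site". Progression has its own retention rule: "for retention rate, progression to definitive RCT will be considered if the estimate is ≥40"%. The section takes 50% as a low true rate and describes the higher one as "80% (a good rate in definitive RCTs").

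**The concern.** Retention is a primary feasibility outcome, and this row turns it into a progression signal. Three features weaken that signal.

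1. Green allows no missing outcome at all, so a rate that the protocol itself calls good gets the same colour as 60%.
2. Each cell gives both a percentage and a count. They agree only when exactly 60 are randomised, although the recruitment row expressly provides for 36 to 59.
3. The lower bands do not fit together, and they do not fit the 40% rule in the Sample size section.

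At stake is whether the feasibility team can read one unambiguous colour from the retention result, and whether a recruitment problem could be reported a second time as a retention problem.

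**Working it through.** **Inputs.** Target 60 under 1:1 allocation, so 30 per group (Sample size; Randomisation). Progression considered from 40%; reference true rates 50% and 80%; stated probabilities 0.82 and 1 (Sample size). Bands as printed in Table 2. All calculations are exact binomial.

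**The plan's own figures.** With n = 30 per group, 40% is 12 participants.

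- True rate 80%: P(X ≥ 12) = 1.000, as stated.
- True rate 50%: P(X ≥ 12) = 0.900, P(X ≥ 13) = 0.819, and both groups at 12 or more = 0.900² = 0.810. The stated 0.82 is therefore matched by strictly above 40% in one group, or nearly by both groups reaching 40%, but not by the literal 40% or more in one group. The inputs are confirmed, and nothing below depends on this difference.

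**Green band, 60 randomised.** An observed 80% is 0.80 × 60 = 48, which is amber by count and by percentage. P(green) = p^60:

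| True retention p | P(green) |
|---|---|
| 80% | 0.0000015 |
| 90% | 0.002 |
| 95% | 0.046 |
| 98% | 0.30 |
| 99% | 0.55 |

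An even chance of green needs p = 0.5^(1/60) = 98.9%.

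**Count against percentage, fewer than 60 randomised.**

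- 50 randomised, 50 with the outcome: 100%, green by percentage; 50 falls in 36–59, amber by count.
- 36 randomised, 35 with the outcome: 35/36 = 97%, amber by percentage; 35 is below 36, red by count.

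If the counts govern, the retention needed to avoid red is 36/N:

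| N randomised | Retention needed (36/N) | P(red by count) at true 80% |
|---|---|---|
| 60 | 60% | 0.0001 |
| 50 | 72% | 0.06 |
| 45 | 80% | 0.41 |
| 40 | 90% | 0.92 |
| 36 | 100% | 0.9997 |

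A small shortfall costs little beyond the loss of green. A large one is charged again as poor retention.

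**Red band.** 36/60 = 60%, but the percentage printed beside fewer than 36 is below 50%. Counts of 30 to 35 out of 60 (50% to 58%) are red by count and have no percentage band.

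**The 40% rule.** 40% of 60 is 24, red by count and by percentage. At a true rate of 50% with 60 randomised, P(fewer than 36) = 0.92, and the probability of 24 to 35 (at least 40% overall, yet red by count) is 0.88. The Sample size section treats that same true rate as giving a high chance of going on to the definitive trial.

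**The case against.** The best defence is that the bracketed counts are only the percentages worked out at the planned 60. The Primary outcome measures section makes retention a proportion of participants, and on that reading recruitment is not scored twice. A reader might infer that any recruitment shortfall is automatically scored again as poor retention. The documents do not support that: it happens only if the counts govern, which the table leaves open. Nor do the two readings differ whenever fewer than 60 are randomised. Taking red as below 60% and true retention as 80%, the chance that they differ is about 0.003 at N = 55 and 0.06 at N = 50, reaching 0.41 only at N = 45.

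A reader might also infer that green is unattainable. That is too strong. Deaths within 30 days score 0 on DAOH, so they are not missing, and data are extracted from patient charts, so near-complete capture is plausible. On the other side, Data management stops further collection on withdrawal, and the Eligibility criteria section has patients enrolled through a consultee asked later for permission to continue. One withdrawal before day 30 is enough to lose green, and at true retention 98% green is still missed 70% of the time.

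It is also fair that 80% is described as good for definitive trials and not as this study's threshold, that a strict green bar is a design choice, that amber does not stop the programme, and that the reported rate and CI will still separate excellent from mediocre retention. These points limit the consequence. They do not resolve the conflict between count and percentage, the mismatched red cell, or the 40% rule that lies inside red.

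**Conclusion.** The point holds as an internal inconsistency in a progression criterion, of moderate consequence. On any reading an observed 80% is amber, and with 60 randomised green is unlikely unless true retention is close to 99%. With fewer than 60 randomised, some results get two colours; the conflict is rare for small shortfalls and serious from about N = 45 downward if the counts govern. Independently of recruitment, 50–59% has no percentage band, and the Sample size section would consider progression at rates that Table 2 labels likely unfeasible. The probabilities assume independent participants with a common retention rate. The direct contradictions need no such assumption.

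**What to change.** - Define retention once, as participants with 30-day DAOH known divided by participants randomised. Align the list of primary objectives, which uses retention for completing the intervention.
- Delete the participant counts from the retention row, so that recruitment is judged only in its own row.
- Make the percentage bands contiguous, and reconcile them with the 40% rule in the Sample size section so that one progression threshold applies.
- Set a green bar below 100% before outcome data are reviewed. One option is 80% or more, using the protocol's own description of a good rate. With 60 randomised (48 or more), P(green) would be 0.58 at true 80%, 0.89 at 85% and 0.99 at 90%. The exact cut-off is a judgement for the steering group.

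The cost is one table row, matching sentences in the Sample size section and the objectives, and steering-group sign-off; no extra data are collected. The downside is that a prespecified green bar is relaxed. Recruitment was planned for 1 May 2024 to 31 January 2025 and the reported protocol version is dated 3 October 2024, so the change should be dated and reported, with the printed bands shown beside the new ones.

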Proportion of patients agreeing to take part out of all those invited (recruitment rate).Proportion of participants who complete the intervention (retention rate).Percentage of intervention sessions completed (intervention fidelity).Intervention acceptability to participants and service providers.

The secondary objectives are

To evaluate a range of clinical and patient-reported outcome measures to aid selection of the most appropriate primary outcome measure for a definitive trial, with estimates for sample size calculation and health economic evaluations of any future definitive trial.

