### Intervention

The intervention consists of a combination of structured, individualised physiotherapy and optimised nutrition, beginning immediately following recruitment and continuing for up to 14-days or hospital discharge, whichever is sooner. The physiotherapy or nutritional intervention will be terminated early if no longer deemed to be clinically required or appropriate (eg, patent deterioration and receiving end-of-life care; enteral nutrition becomes contraindicated).

The enhanced physiotherapy intervention will be delivered by a dedicated team led by a physiotherapist. The intervention comprises (1) completion of a comprehensive physical and non-physical assessment to create an individualised treatment plan, (2) setting of patient-centred rehabilitation goals with regular reassessment, (3) provision of daily physiotherapy (Monday–Friday), targeting the highest level of mobility attainable and delivery of individualised exercise programmes and (4) close working with ward staff to optimise treatment delivery and ensure seamless transitions of care once the enhanced intervention is complete.

The nutritional component will be led by a specialist dietitian. A comprehensive nutritional assessment will be completed on day one of the intervention period to include current nutritional intake from oral diet, nutritional supplements and enteral tube feeding. Indirect calorimetry (QNRG+) will be used where possible to determine resting energy expenditure, and protein requirements will be calculated using weight-based equations. An individualised nutritional plan will be devised, to include dietary modification, additional food provision, prescription of oral nutritional supplements or modification to enteral feeding regimen as required. This may also include prescribed nutritional supplementation used within 2 hours of the physiotherapy session to address the catabolic nature of exercise. Review and adjustment to the nutritional care plan will occur daily (Monday–Friday) throughout the intervention period. At the end of the intervention period, patients will be transferred to standard dietetic care, with a comprehensive handover provided.

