### Outcome measures

#### Primary outcome measures

Recruitment rate, overall and by centre.Retention rate, defined as the proportion of participants that complete the primary outcome.Intervention adherence measured by the proportion of enhanced physiotherapy sessions completed and nutrition delivery compared with targets.Acceptability of the intervention to participants and service providers.

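### The nutrition row of Table 2 scores prescribed supplements taken, while the primary outcome is nutrition delivered against targets; the two can disagree in either direction

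*Protocol article*

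**What the plan says.** The Protocol article describes fidelity or adherence in four places.

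- **Objectives** (end of Rationale for the trial): "Percentage of intervention sessions completed (intervention fidelity"). No nutrition intake measure is named.
- **Primary outcome measures:** "Intervention adherence measured by the proportion of enhanced physiotherapy sessions completed and nutrition delivery compared with targets".
- **Data analysis, text:** fidelity is assumed if 70% of planned sessions are completed. No nutrition rule is given.
- **Data analysis, Table 2:** one row for physiotherapy sessions and a separate row, "Intervention fidelity (nutrition)Proportion of prescribed supplements taken", with green above 70%, amber 40–70% and red below 40%.

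The Intervention section describes an individual plan "to include dietary modification, additional food provision, prescription of oral nutritional supplements or modification to enteral feeding regimen as required". On supplements around exercise it says: "This may also include prescribed nutritional supplementation used within 2 hours of the physiotherapy session". The day-one assessment covers "current nutritional intake from oral diet, nutritional supplements and enteral tube feeding". For requirements, indirect calorimetry "will be used where possible to determine resting energy expenditure, and protein requirements will be calculated using weight-based equations". Table 1 includes nutrition and calories consumed in the daily record, for up to 14 days.

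**The concern.** The physiotherapy row of Table 2 matches its primary outcome, since both count sessions completed. The nutrition row does not. The outcome compares what was delivered with what the participant needed, whereas the row compares supplements taken with supplements prescribed. Numerator and denominator both differ, and nothing in the article links them.

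This is a conflict between printed definitions, not a detail left to a fuller document. Eligible patients are those who cannot cover their nutritional needs unaided, and the trial's hypothesis is that exercise and adequate nutrition must be combined. Whether the nutrition half can be delivered on the ward is therefore a central feasibility question, and one of the four progression rows answers a different one. A false green could carry an under-delivered intervention into a definitive trial. A false red could mark a deliverable one as probably unfeasible.

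**Working it through.** **No figure to reproduce.** The article gives no calculation for the nutrition criterion. The check sets the definitions side by side and then illustrates how far they can part.

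**Step 1: what each measure covers.** The plan can use "dietary modification, additional food provision, prescription of oral nutritional supplements or modification to enteral feeding regimen as required".

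| Route | Counted in delivery against target | Counted in the Table 2 row |
|---|---|---|
| Dietary modification | yes | no |
| Additional food | yes | no |
| Oral nutritional supplements | yes | yes |
| Tube feed | yes | not on the natural reading |

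The day-one assessment lists supplements and tube feeding as separate sources, which is why tube feed is not naturally a supplement. If it were counted as one, the first two routes would still be missed.

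**Step 2: participants with no supplement.** The routes are used as needed and the exercise-related supplement is optional, so a participant can follow the plan fully with none prescribed. In a per-participant ratio that person contributes 0/0. In a pooled ratio (all taken divided by all prescribed) that person adds nothing to either part, and the row describes only the remainder of the arm. The article does not say which ratio is meant.

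**Step 3: how far the measures can differ.** Let

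- s = share of the target prescribed as supplements,
- u = proportion of those supplements taken (the Table 2 measure),
- f = proportion of the remaining target delivered by food and tube feed.

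Then delivery ÷ target = s·u + (1 − s)·f. The documents give none of s, u or f; all values below are assumptions.

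| s | u | f | Table 2 row | Delivery ÷ target | Delivery on the same bands |
|---|---|---|---|---|---|
| 0.2 | 0.80 | 0.50 | 80%, green | 0.16 + 0.40 = 56% | amber |
| 0.1 | 1.00 | 0.30 | 100%, green | 0.10 + 0.27 = 37% | red |
| 0.2 | 0.30 | 0.95 | 30%, red | 0.06 + 0.76 = 82% | green |
| 0 | 0/0 | f | undefined | f | defined |

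**Step 4: a range.** With s = 0.1, 0.2, 0.3, 0.5; f = 0.3, 0.5, 0.6; and u = 0.71, 0.80, 1.00, there are 4 × 3 × 3 = 36 combinations, all green in Table 2. Delivery runs from 34% to 80%. It exceeds 70% in three of them (72%, 75% and 80%) and is at or below 70% in the other 33. In the other direction, with u = 0.30 and f = 0.95, delivery is 88.5%, 82% and 75.5% at s = 0.1, 0.2 and 0.3, while Table 2 is red each time.

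**Step 5: when they agree.** If u is above 0.70 and f is at least 0.70, the weighted average is above 0.70 whenever s is above zero, so both are green. A false green therefore needs f below 0.70. The grid in step 4 was set in that region, so 33 of 36 shows what is possible and is not a probability.

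**The case against.** Four points can fairly be made for the plan.

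1. **Delivery is not abandoned.** A reader might infer that Table 2 replaces the primary outcome and hides underfeeding. The documents do not support that. Delivery against targets is still listed as a primary outcome and intake is recorded daily, so those deciding on progression should see both results. The mismatch is confined to one row.
2. **Table 2 is not binding.** A reader might take it as a strict go/no-go rule. Its title speaks of determining progression, but the text calls it a guide, and acceptability is also assessed through interviews.
3. **The criterion as a whole is not undefined.** The 0/0 arises only per participant. A pooled ratio fails only if nobody is prescribed a supplement. What stands is that such participants go uncounted and the article does not say which ratio applies.
4. **The numbers are assumed and describe single participants.** Table 2 judges the intervention arm, about 30 people, and plans are reviewed each weekday, which makes persistently low delivery less likely. A reader might infer that the row would mislead in this trial, or that it would be met by prescribing few supplements. Nothing in the documents shows either.

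A measure based on targets also has its own gap: calorimetry is used only where possible, the article gives no energy target for the other participants, and it does not say that measured resting expenditure is itself the target. Table 1 does not name protein. These points limit the strength of the finding and shape the fix, but they do not reconcile the definitions.

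**Conclusion.** The point holds as an inconsistency between definitions. The primary outcome, the Table 2 row, and the session-only wording in the objectives and in the 70% rule do not describe the same thing. Because supplements are one route among several, the Table 2 colour can differ from the stated primary outcome in both directions, and participants without a supplement are either uncounted or undefined.

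The size is unknown. The illustrations (100% against 37%, and 30% against 82%) rest wholly on assumed s, u and f, and on applying the 40% and 70% bands to delivery. They show that disagreement is possible, not that it is expected. The plan should be corrected, because one of four progression rows does not measure its declared outcome and the remedy is cheap. The point does not undermine the trial.

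**What to change.** Make the nutrition row of Table 2 the outcome given under Primary outcome measures: energy and protein delivered from all routes, as a percentage of the individual target over intervention days, averaged per participant. In addition:

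- state in advance which of energy and protein sets the colour, for example the lower of the two;
- state how the energy target is defined, including the one used when calorimetry is not possible;
- confirm that the 40% and 70% bands suit delivery against target, since they were set for supplement uptake;
- confirm that the daily intake record captures protein as well as calories;
- align the fidelity wording in the objectives and in the Data analysis text with the same definition;
- keep supplement uptake as a descriptive item with a stated denominator.

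The cost is a revised table row, matching edits in two other places and a small amount of derivation. Intake is already recorded daily and requirements are assessed on day one, so no new visit or change in sample size is needed. If protein is not captured now, one data item must be added. The resulting percentage may be lower than supplement uptake.

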### Patient and public involvement (PPI)

We have planned full involvement across the research cycle. We have collaborated with patient partners to ensure the study addresses key needs that are currently missing from routine care in the recovery of patients following critical illness and that the design is appropriate for potentially anxious and functionally impaired patients. We have identified PPI co-applicants through ICU steps (national patient support group) and the University Hospitals Coventry & Warwickshire PPI group. Both groups expressed strong support for the proposal. Our PPI co-applicants have helped develop the plain English summary, inclusion criteria, personalised intervention and proposed outcomes. Our PPI work has indicated that returning to work (or usual activities) is important in this group. For this reason, our feasibility study will work with our PPI collaborators to develop an acceptable method for capturing this outcome within a future definitive study. We will also work with our PPI group to inform the time points for data collection. They will be full members of the trial team and will assist with analysis and interpretation of the acceptability data (research methods training will be offered), as well as advise on trial delivery and dissemination. All involvement will be reported in the final study report.

## 
Ethics and dissemination

The study has received a favourable ethical approval from the Wales Research and Ethics Committee 2 (24/WA/0050). Health Research Authority approval was obtained on the 12 March 2024. This paper reports protocol version 2.0 (03 October 2024) and has been written with reference to the Standard Protocol Items: Recommendations for Interventional Trials checklist.^34^

Results from this study will be disseminated at regional and international conferences and in peer-reviewed journals. Authorship of any papers related to this study will follow the ICMJE recommendations (http://www.icmje.org/recommendations/).
